|--|-------------------------------------------------------------------------------------------------------------------------------------------------------------------------------------------------------------------------------------------------------------------------------------------------------------------------------------------------------------------------------------------------------------------------------------------------------------------------------------------------------------------------------------------------------------------------------------------------------------------------------------------------------------------------------------------------------------------------------------------------------------------------------------------------------------------------------------------------------------------------------------------------------------------------------------------------------------------------------------------------------------------------------------------------------------------------------------------------------------------------------------------------------------------------------------------------------------------------------------------------------------------------------------------------------------------------------------------------------------------------------------------------------------------------------------------------------------------------------------------------------------------------------------------------------------------------------------------------------------------------------------------------------------------------------------------------------------------------------------------------------------------------------------------------------------------------------------------------------------------------------------------------------------------------------------------------------------------------------------------------------------------|

|  |                                                                                                                                                                                                                                                                                                                                                                                                                                                                                                                                                                                                                                                                                                                                                                                                                                                                                                                                                                                                                                                                                                                                                                                                                                                                                                                                                                                                                                                                                                                                                                                                                                                                                                                                                                                                                                                                                                                                                                                                                                                                                                                                                                                                                                                                                                                                                                                                                                                                                                                                                                                                                                                                                                                     |
|--|---------------------------------------------------------------------------------------------------------------------------------------------------------------------------------------------------------------------------------------------------------------------------------------------------------------------------------------------------------------------------------------------------------------------------------------------------------------------------------------------------------------------------------------------------------------------------------------------------------------------------------------------------------------------------------------------------------------------------------------------------------------------------------------------------------------------------------------------------------------------------------------------------------------------------------------------------------------------------------------------------------------------------------------------------------------------------------------------------------------------------------------------------------------------------------------------------------------------------------------------------------------------------------------------------------------------------------------------------------------------------------------------------------------------------------------------------------------------------------------------------------------------------------------------------------------------------------------------------------------------------------------------------------------------------------------------------------------------------------------------------------------------------------------------------------------------------------------------------------------------------------------------------------------------------------------------------------------------------------------------------------------------------------------------------------------------------------------------------------------------------------------------------------------------------------------------------------------------------------------------------------------------------------------------------------------------------------------------------------------------------------------------------------------------------------------------------------------------------------------------------------------------------------------------------------------------------------------------------------------------------------------------------------------------------------------------------------------------|
|  | 
De nul- en nameting voor PMers bestaat uit: / The baseline and close out measurements for ECEC teachers will consist of:
 
 
- Het invullen van een vragenlijst (Gubbels, Sleddens, Raaijmakers, Gies, & Kremers, 2015) gericht op kennis, attitude en vaardigheden t.a.v. een gezonde leefstijl. In de vragenlijst komt het vertrouwen van PMers in het goed kunnen ondersteunen van kinderen en hun ouders/verzorgers bij een gezonde leefstijl aan bod. Tevens worden bij de nulmeting in deze vragenlijst enkele demografische kenmerken nagevraagd. / Questionnaires about knowledge, attitude and practices regarding a healthy lifestyle. In the questionnaires also the level of confidence of ECEC teachers in supporting children and their parents/caregivers in pursuing a healthy lifestyle will be checked. Furthermore, demographic characteristics will be obtained at baseline.
 
- Het meten van lengte en gewicht (voor het berekenen van de BMI). / Height and weight measurements (to calculate BMI).
 
- Het meten van lichaamssamenstelling middels Bio-elektrische Impedantie Analyse (BIA). / Body composition measurements via Bioelectrical Impedance Analysis (BIA).
 
- Het invullen van een 3 daags eetdagboek. / 3-day food records.
 
- Het invullen van een 3 daags beweegdagboek. / 3-day physical activity records.
 
- Het meten van fysieke activiteit op 7 dagen met een Physical Activity Monitor (PAM). / Physical activity measurements via a Physical Activity Monitor (PAM) – 7 days.
 
 
Getrainde studenten van de HvA meten lengte, gewicht en lichaamssamenstelling van een PMer op de voorschool-locatie zelf. / Trained students of the AUAS will measure height, weight and body composition of the ECEC teachers at preschool. Na de metingen wordt op papier een vragenlijst en eet- en beweegdagboek met bijhorende informatie verstrekt. / After the measurements, a questionnaire, food record and physical activity record will be provided on paper. Daarnaast wordt een PAM meegegeven. / Furthermore, a PAM will be given. Na een week haalt een student de vragenlijst, de PAM, het eetdagboek en het beweegdagboek op bij de voorschool-locatie. / After a week, a student will pick up the questionnaire, PAM, food record and physical activity record at preschool. Hierbij controleert de student de ingevulde vragenlijsten op volledigheid. / The student will check if a questionnaire is completed.
 |
|--|---------------------------------------------------------------------------------------------------------------------------------------------------------------------------------------------------------------------------------------------------------------------------------------------------------------------------------------------------------------------------------------------------------------------------------------------------------------------------------------------------------------------------------------------------------------------------------------------------------------------------------------------------------------------------------------------------------------------------------------------------------------------------------------------------------------------------------------------------------------------------------------------------------------------------------------------------------------------------------------------------------------------------------------------------------------------------------------------------------------------------------------------------------------------------------------------------------------------------------------------------------------------------------------------------------------------------------------------------------------------------------------------------------------------------------------------------------------------------------------------------------------------------------------------------------------------------------------------------------------------------------------------------------------------------------------------------------------------------------------------------------------------------------------------------------------------------------------------------------------------------------------------------------------------------------------------------------------------------------------------------------------------------------------------------------------------------------------------------------------------------------------------------------------------------------------------------------------------------------------------------------------------------------------------------------------------------------------------------------------------------------------------------------------------------------------------------------------------------------------------------------------------------------------------------------------------------------------------------------------------------------------------------------------------------------------------------------------------|

De tussenmeting voor PMers bestaat uit: / **The follow-up measurements for ECEC teachers will consist of:**

- Het invullen van een vragenlijst (Gubbels, Sleddens, Raaijmakers, Gies, & Kremers, 2015) gericht op kennis, attitude en vaardigheden t.a.v. een gezonde leefstijl . In de vragenlijst komt het vertrouwen van PMers in het goed kunnen ondersteunen van kinderen en hun ouders/verzorgers bij een gezonde leefstijl aan bod. / **Questionnaires about knowledge, attitude and practices regarding a healthy lifestyle. In the questionnaires also the level of confidence of ECEC teachers in supporting children and their parents/caregivers in pursuing a healthy lifestyle will be checked.**
- Het meten van lengte en gewicht (voor het berekenen van de BMI). / **Height and weight measurements (to calculate BMI).**
- Het meten van lichaamssamenstelling middels BIA. / **Body composition measurements via Bioelectrical Impedance Analysis (BIA).**

Getrainde studenten van de HvA meten lengte, gewicht en

lichaamssamenstelling van een PMer op de voorschool-locatie zelf. /

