|  | 
research question, 120 ECEC teachers will be included (60 ECEC teachers in the intervention group and 60 ECEC teachers in the control group).
 
De sample grootte is gebaseerd op een medium effect grootte (Cohen's d: 0.50), een 1-zijdige alpha van 5%, en een power van 80%. Daarnaast is er gecorrigeerd voor
                                                                                                                                                                                                                                                                                                                                                                                                                                                                                                                                                                                                                                                                                                                                                                                                                                                                                                                                                                                                                                                                                                                                                                                                                                                                                                                                                                                                                                                                                                                            |

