|  | 
het design effect (gemiddelde cluster grootte: 3, ICC: 0.05) en rekening gehouden met 10% uitval. / The sample size is based on a medium effect size (Cohen's d: 0.50), a 1-sided alpha of 5% and a power of 80%, taken into account a design effect (mean cluster size = 3, ICC: 0.05) and a 10% drop-out rate. Om antwoord te geven op de secundaire onderzoeksvragen worden per PMer 2 kinderen en hun ouders/verzorgers geïnccludeerd. In totaal gaat het om 240 kinderen en hun ouders/verzorgers (120 kinderen en hun ouders/verzorgers in de interventiegroep en 120 kinderen en hun ouders/verzorgers in de controlegroep). / To answer the secondary research questions, per ECEC teacher, 2 children and their parents/caregivers will be included. In total, it concerns 240 children and their parents/caregivers (120 children and their parents/caregivers in the intervention group and 120 children and their parents/caregivers in the control group). Met 120 kinderen per groep is het mogelijk om, met een 2-zijdige alpha van 5% en een power van 80%, een klein tot medium effect grootte (Cohen's d: 0.35-0.40) aan te tonen. / With 120 children per group, it is possible to show, with a 2-sided alpha of 5% and a power of 80%, a small to medium effect size (Cohen's d: 0.35 - 0.40). Dit beoogde aantal kinderen is vergelijkbaar met de sample grootte van een gecombineerde voedings- en beweeginterventie waar na 7 maanden follow-up een significant verschil in BMI z-score werd aangetoond tussen de interventie- en controlegroep (Alkon et al., 2013). / This sample size is comparable to the sample size of a combined nutrition and physical activity intervention where a significant difference in BMI z-score was found between the intervention and control group after 7 months of follow-up.
 |

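### The effect stated as detectable in children (d 0.35 to 0.40) has no stated basis: 0.35 is out of reach even without clustering, and with about 6 children per preschool and the teacher ICC and drop-out carried over the figure is about 0.43

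*Protocol*

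**What the plan says.** All the figures stand in the Sample size row of the Protocol (Information about the study).

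- **Teachers (primary outcome).** The calculation targets d = 0.50 with 80% power at a one-sided 5% level. Clustering and loss are both allowed for: "taken into account a design effect (mean cluster size = 3, ICC: 0.05) and a 10% drop-out rate". The result is "60 ECEC teachers in the intervention group and 60 ECEC teachers in the control group".
- **Children (secondary outcomes).** "per ECEC teacher, 2 children and their parents/caregivers will be included", which makes 240 children, 120 per group. The protocol then states: "With 120 children per group, it is possible to show, with a 2-sided alpha of 5% and a power of 80"%, a Cohen's d of 0.35 to 0.40.

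The sentence on children names no cluster size, ICC or drop-out rate. The Study design row makes the preschool the unit of randomisation. The Statistical analysis row plans a multi-level analysis that allows for dependence within preschools.

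**The concern.** The teacher number is corrected for clustering and loss, and the protocol shows the inputs. The next sentences give a detectable effect for children in the same preschools and show none. Children are the larger cluster: each preschool supplies about three teachers but about six children, so the same ICC costs more information in children than in teachers.

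The stated range describes how sensitive the trial is for the child part of the secondary objective: BMI, body composition, eating behaviour and physical activity. If the figure is too favourable, a reader of a null result in children could take effects of 0.35 to 0.40 as fairly well excluded when the chance of missing them is above the 20% that the sentence implies.

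**Working it through.** **Inputs from the Sample size row.** 120 children per group; two-sided alpha 5%; power 80%; 2 children per teacher. For teachers: mean cluster size 3, ICC 0.05, drop-out 10%, d = 0.50, one-sided alpha 5%, power 80%, 60 per group.

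**Assumptions, because the protocol gives no child values.** Child ICC 0.05 and child drop-out 10%, both carried over from the teacher calculation; a range of ICC is shown below.

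**Formulas.**
- Design effect: DE = 1 + (m − 1) × ICC, with m the number per preschool.
- Effective number per group: n_eff = n × (1 − drop-out) / DE.
- Detectable effect: d = (1.960 + 0.8416) × √(2 / n_eff) = 2.8016 × √(2 / n_eff).

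**Step 1: reproduce the teacher number.** 2 × ((1.645 + 0.8416) / 0.50)² = 49.5 per group. DE = 1 + 2 × 0.05 = 1.10. Then 49.5 × 1.10 / 0.9 = 60.5, against 60 stated. The teacher calculation reproduces.

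**Step 2: the children's range with no adjustment.** 2.8016 × √(2 / 120) = 0.362, inside the stated range. Power at d = 0.35 is 77%. Reaching 80% at 0.35 takes 2 × (2.8016 / 0.35)² = 128.1 independent children per group, more than the 120 planned.

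**Step 3: cluster size for children.** 3 teachers × 2 children = 6 per preschool, so DE = 1 + 5 × 0.05 = 1.25.

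**Step 4: detectable effect under each adjustment (ICC 0.05).**

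| Adjustment | n_eff per group | Detectable d | Power at 0.35 | Power at 0.40 |
|---|---|---|---|---|
| None | 120 | 0.362 | 77% | 87% |
| 10% loss only | 108 | 0.381 | 73% | 84% |
| DE 1.10 only | 109.1 | 0.379 | 73% | 84% |
| DE 1.10 and 10% loss | 98.2 | 0.400 | 69% | 80% |
| DE 1.25 only | 96 | 0.404 | 68% | 79% |
| DE 1.25 and 10% loss | 86.4 | 0.426 | 63% | 75% |

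With the t distribution the last row becomes d = 0.429, with power 63% at 0.35 and 74% at 0.40. If loss also shrinks the cluster to 5.4 children, DE = 1 + 4.4 × 0.05 = 1.22, n_eff = 88.5 and d = 0.421. Hence 0.42 to 0.43.

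**Step 5: sensitivity to the child ICC (6 per preschool, 10% loss).**

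| ICC | 0 | 0.01 | 0.02 | 0.03 | 0.05 | 0.10 |
|---|---|---|---|---|---|---|
| Detectable d | 0.381 | 0.391 | 0.400 | 0.409 | 0.426 | 0.467 |

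After 10% loss, 0.40 is kept up to an ICC of about 0.02. The value 0.35 is reached in no column.

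**The case against.** The strongest reply is that the protocol may already have allowed for clustering and loss. A reader might infer from the silence that both were left out. The document does not show that: the unadjusted calculation gives 0.36 and does not explain an upper end of 0.40, whereas the printed teacher design effect of 1.10 with 10% loss gives 0.400. This stands, so omission cannot be asserted. It does not rescue the figure, because on that reading a cluster size of 3 was applied to children who number about 6 per preschool.

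Second, 0.43 uses an ICC and a drop-out rate that the protocol gives for teachers only. This also stands. A reader might take 0.43 as what the design delivers, but it is a conditional figure. With a child ICC of 0.02 or less, 0.40 survives 10% loss; with ICC 0.05 and no loss, d is 0.404, practically the stated upper end.

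Third, the check compares two means at one time point, while children are measured at baseline and close-out. If baseline were used as a covariate, an assumed correlation of 0.35 would multiply 0.426 by √(1 − 0.35²) = 0.94 and return it to about 0.40. The protocol does not settle this and claims no such gain, but the restated figure should name its basis.

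Fourth, the number of children follows from two per teacher and was not derived from the effect size, and the planned analysis already handles clustering. This stands too: standard errors and type I error are not in question, only the stated sensitivity.

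**Conclusion.** The stated range is not supported as written. Its lower end, 0.35, fails with no borrowed assumption: 120 independent, fully observed children per group detect 0.36. Its upper end, 0.40, holds at ICC 0.05 with 10% loss only if the teacher cluster size of 3 is used for children. With about 6 children per preschool and the teacher ICC and drop-out assumed for them, the detectable effect is 0.42 to 0.43. At a true d of 0.35 the chance of missing it is then about 37%, and at 0.40 about 25%, rather than 20%.

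The severity is minor to moderate. The excess over 0.40 is 0.02 to 0.03 and concerns secondary outcomes. A reader might conclude that the trial as a whole is too small; the document does not support that, since the teacher calculation reproduces and is unaffected. Nor does the protocol say that a null result in children would be read as excluding 0.35 to 0.40; that risk lies with later readers.

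**What to change.** Keep 240 children and replace the sentence on the detectable effect with one that names its inputs, for example: *With 120 children per group, about 6 per preschool, an assumed ICC of 0.05 and 10% loss, a difference of about d = 0.43 can be detected with 80% power at two-sided alpha 5%, without baseline adjustment; the figure is 0.39 at ICC 0.01 and 0.47 at ICC 0.10.* If the sponsor has a child ICC or drop-out rate of its own, it should state that and recompute by the same formula.

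The comparison with the cited trial's sample size can stay, as a remark beside the calculation. The cost is one sentence and a slightly less favourable figure, with no extra participants and no change to the teacher number.
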